#### Covariates

The following covariates will be assessed: (1) socio-demographic characteristics (gender, age, education, employment status, nationality, marital status), (2) smoking-related variables (use of other tobacco products, years smoking, number and frequency of previous quit attempts [42], confidence in quitting and importance to quit, craving [43], other smoking household members, smoking behaviour of the partner, use of and adherence to additional supportive materials (e.g., NRT, pharmacotherapy, e-cigarettes, heat-not-burn products)), (3) health status (depressive symptoms [44], selected smoking-related illnesses, mental comorbidity), (4) received social support (supportive network and overall quitting support [45]), and (5) the use and acceptability of the received intervention (telephone counselling or self-help brochure) [31].

### Data collection and management

Participants will be recruited consecutively between October 2021 and June 2022. Therefore, data collection will take place at different time points (at baseline, three months and twelve months after baseline assessment) over a period of approximately two years. Data will be collected via online questionnaires using the software SoSci Survey [46]. It is expected that the majority of questionnaires will be administered digitally (compared to phone interviews). In order to biochemically verify abstinence, 20% of study participants who will report abstinence at 12-month follow-up and who consented to participate will be randomly selected. Research staff will meet participants at their preferred location and will collect breath carbon monoxide (CO) using a portable CO monitor.

Once a participant is enrolled, the study site will make every reasonable effort to follow the participant for the entire study period. Various procedures will be used to reduce attrition, including reminder emails and calls, flexible scheduling of the counselling sessions, and incentives for completing the questionnaires. It is expected that the rate of loss-to-follow-up will not exceed the calculated 30%. To enhance validity of data, multiple methods will be used to assess intervention adherence including the phone call prior to enrolment in order to answer possible questions and questionnaire items on the use and acceptability of the received intervention at 3-month post assessment.

All participant data is handled in accordance with the General Data Protection Regulation (GDPR). All data will be maintained confidentially before, during, and after the trial and is stored securely at the study site with access only by dedicated study team members. All substantial procedures are described in the application for the Ethics Committee and can be provided on request. The final data set will be stored for 10 years after completion of the study. A data monitoring committee is not considered necessary as participants are not blinded to the study conditions and as this is a short-term, non-invasive intervention with the opportunity to quit at any time without any negative consequences or side-effects.

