**ASSESSMENTS:**							
**Socio-demographic characteristics**	X	X					
**Smoking-related variables**		X			X	X	
**Health status**		X			X		
**Received social support**					X		
**7-day point prevalence abstinence**					X	X	
**Prolonged abstinence**						X	
**Number of cigarettes smoked per day**	X	X			X	X	
**Nicotine dependence**		X			X	X	
**Number and duration of quit attempts**					X	X	
**Occurrence of abstinence of at least 24 hours**					X	X	
**Motivation to quit**	X	X			X	X	
**Implementation of smoking restrictions at home**		X			X	X	
**Smoking-related cognitions**		X			X		
**Coping strategies**		X			X		
**Use and acceptability of the received intervention**					X		
**Breath carbon monoxide (CO)**							X

Note: -t2: recruitment of participants by a market research company using a screening questionnaire; −t1: baseline assessment; 0: randomization of participants to either the intervention or control condition; t1: intervention (telephone counselling or self-help broschure); t2: post assessment 3 months after baseline assessment; t3: follow-up assessment 12 months after baseline assessment; t4: biochemical verification: 20% random sample of participants who reported 7-day point prevalence abstinence at 12-month assessment

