#### Primary outcomes

In accordance with the Russell standard criteria [28], primary outcome measures will include (1) seven-day point prevalence abstinence at 3-month post and 12-month follow-up assessment, (2) prolonged abstinence (abstinence over the 12 month period allowing up to five cigarettes in total), and (3) biochemical verification of abstinence in 20% of the abstainers at 12-month follow-up. To define abstinence, cut-off scores of 8 ppm for CO will be used [29].

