The current study is the first to examine the effectiveness of the national German Smokers Quitline using a randomized design with post and follow-up assessments allowing to test the short- and long-term effects of the intervention. The assessment of abstinence at twelve-month follow-up is recommended as it is more closely related to life-long abstinence and false-positive results are less likely [49]. Another strength of the current study lies in the application of RS criteria for trials of cessation aids [28, 50], which enhances the quality of the data and the generalizability of the results. One limitation of this study is the assessment of abstincence via self-reports, although self-reports have previously been shown to be reliable and valid measures of respondents’ smoking behaviour [51]. Additionally, in a subsample of all study participants who report 7-day point prevalence at follow-up, smoking cessation will be biochemically verified to counteract reporting biases [29, 31]. Another limitation of this study is that participants will be recruited via an online panel, which may limit the generalizability of study results.

Quitlines are considered an important and cost-effective population-based tobacco control strategy [17]. However, of the 19.9% of German current and recent former smokers who try to quit smoking per year, only 13.0% use at least one evidence-based method to support their cessation attempt. The majority of smokers does not make use of quitlines; they reach only about 0.8% of individuals who make a quit attempt [52]. If the intervention provided by the national German Smokers Quitline is found to be effective, awareness should be enhanced to exploit the proportion of smokers that are advised to stop smoking through telephone counselling. Its population-based impact, which means an increased use of the quitline services, could be expanded by communication campaigns. The recruitment for quitline services can be further enhanced by targeting populations that have a high tobacco use prevalence [17]. The results of the current study will provide insights into the effectiveness of the national German Smokers Quitline.

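### Breath CO is taken after the 12-month self-report with no smoking report scheduled beside it, so a raised reading cannot be assigned to a false report rather than to smoking since then

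*Protocol article*

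**What the plan says.** Table 1 separates the 12-month questionnaire ("t3: follow-up assessment 12 months after baseline assessment") from the breath test ("t4: biochemical verification: 20% random sample of participants who reported 7-day point prevalence abstinence at 12-month assessment"). The order is therefore self-report, selection, visit. Data collection and management adds that "20% of study participants who will report abstinence at 12-month follow-up and who consented to participate will be randomly selected", followed by the visit: "Research staff will meet participants at their preferred location and will collect breath carbon monoxide (CO) using a portable CO monitor". Most self-reports are given remotely: "It is expected that the majority of questionnaires will be administered digitally (compared to phone interviews".

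In the t4 column of Table 1, two rows are marked: informed consent and breath CO. Seven-day abstinence, cigarettes per day and the smoking-related variables (which, under Covariates, include other tobacco products) are marked at t2 and t3 but not at t4.

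The article gives the CO result three tasks:
- Study design: to allow correction for overreported abstinence.
- Primary outcomes: verification is item (3), with the statement "To define abstinence, cut-off scores of 8 ppm for CO will be used".
- Discussion: in a subsample, "smoking cessation will be biochemically verified to counteract reporting biases".

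The article gives no t3-t4 interval and no rule for how a reading above the cut-off enters an analysis.

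**The concern.** Overreporting is a property of the statement made at t3. The CO reading is a property of the participant at t4. To get from the second to the first, one must know what the participant says about smoking at t4 and between the two dates. The schedule shows nothing collected for that purpose.

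A raised reading then has at least three explanations: the t3 report was false, it was true and the participant has since relapsed, or another combusted product has been used since t3. Only the first is overreporting.

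This matters because neither participants nor staff are blinded, and the breath test is the only objective check on self-report. If its result is ambiguous, primary outcome (3) and any correction built on it are ambiguous too. The information cannot be recovered after the visit.

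**Working it through.** The plan states no figure on this point, so there is none to reproduce. The steps below size the problem.

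**1. How many people are tested.** Inputs from the article: 910 enrolled (Sample size calculation), a 20% sample (Table 1 note), and long-term quit rates of 7% and 10% (Background, from the cited systematic review).

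Number tested = 0.20 × 910 × quit rate
- at 7%: 0.20 × 63.7 = 12.7, about 13
- at 10%: 0.20 × 91.0 = 18.2, about 18

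This is both arms together. It is smaller if the 20% is drawn only from those who consent, and larger if 7-day abstinence turns out to be more common than the cited rates.

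**2. Weight of one ambiguous case.** 1/18 = 5.6 and 1/13 = 7.7 percentage points.

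**3. Apparent overreporting from relapse alone.** Assumptions, none in the documents: a share o of t3 reports is false, true abstainers relapse at weekly rate r, the visit is d weeks after t3, and CO detects a current smoker with probability s = 0.9.

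Apparent rate = [o + (1 − o) × (1 − (1 − r)^d)] × s

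| r per week | d (weeks) | o = 0 | o = 10% |
|---|---|---|---|
| 1% | 1 | 0.9% | 9.8% |
| 2% | 2 | 3.6% | 12.2% |
| 2% | 4 | 7.0% | 15.3% |
| 5% | 4 | 16.7% | 24.0% |

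Worked line: r = 2%, d = 2, o = 0 gives (1 − 0.98²) × 0.9 = 0.0396 × 0.9 = 3.6%. Without any delay, the two columns would read 0% and 9.0%. The excess is negligible for a prompt visit and large only for a long delay with a high relapse rate.

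**4. What a reading below the cut-off can show.** The documents do not say how far back CO reaches. Assume first-order decay, a half-life of 2 to 8 h and a starting level of 10 to 40 ppm.

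Hours to reach 8 ppm = half-life × log2(starting level / 8)
- shortest: 2 × log2(10/8) = 0.6 h
- middle: 4 × log2(20/8) = 5.3 h
- longest: 8 × log2(40/8) = 18.6 h

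The longest is 18.6/168 = 11% of a seven-day window. On this range, a reading below 8 ppm is compatible with smoking within the previous seven days.

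**The case against.** The strongest reply is that this is an article. The visit window, time of day and a short visit form are details that a full protocol commonly holds, and the article refers to the ethics application for its procedures. That stands for the window and time of day: their absence is no error. It has less force for the smoking report. Table 1 is detailed enough to mark consent at t4, and it marks repeated smoking items elsewhere but not there.

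Stronger readings are tempting, and the documents do not support them:
- *A raised CO will be counted as overreporting and a pass as proof of seven smoke-free days.* No rule says so. The article states the aim of correction without a definition.
- *The reading concerns a different week from the report.* Table 1 gives order, not distance. If visits are prompt, step 3 shows little bias.
- *CO reflects only a few hours.* This is an outside premise. On the assumed range the look-back runs from under one hour to about 19.
- *The verification is worthless, or the trial's main result is biased.* A low failure rate after prompt visits would still inform. Statistical analyses bases the intention-to-treat comparison on all randomised participants, apart from deaths and untraceable moves. Undetermined status counts as smoking, and no CO-based reclassification is described. No difference between arms in this error has been shown.

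Other tobacco use is collected up to t3, which explains some raised readings. It does not cover use after t3.

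**Conclusion.** The point holds in a limited form. Under the schedule as printed, a raised CO at t4 cannot be assigned to a false t3 report rather than to relapse or use of another combusted product since then. That weakens primary outcome (3) and any overreporting correction derived from it, and leaves the main comparison of self-reported abstinence untouched.

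The weight of a single case, about 6 to 8 percentage points, follows from the article's own numbers if 12-month abstinence is near the cited 7 to 10%. The size of the bias cannot be stated without the delay; the 0.9% to 16.7% range for relapse alone rests on assumed relapse rates, delays and sensitivity. The limit on what a pass can show rests on the assumed CO decay. The change is worth making because it is cheap and the information is lost once the visit is over.

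**What to change.** At the t4 visit, immediately before the breath test, record 7-day smoking status, date and time of the last cigarette, date of any return to smoking since t3, and use of other combusted products. Add these items to the t4 column of Table 1.

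Report three groups separately:
- A: CO at or above the cut-off, same-day claimed abstinence, no other combusted product
- B: admitted smoking dated after t3
- C: admitted smoking that contradicts the t3 report

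List raised readings accompanied by another combusted product as indeterminate.

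Give the overreporting rate as a range, from (A + C)/n with group B taken as true relapse to (A + B + C)/n with group B taken as misreporting. For example, with n = 16, A = 1, B = 1 and C = 0, the range is 6.3% to 12.5%. Counting group A alone would understate overreporting, because someone who reported falsely at t3 but admits smoking face to face would pass as a later relapse. Report the t3-t4 interval alongside.

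Reword the cut-off sentence under Primary outcomes so that CO supports recent abstinence at the visit and does not by itself confirm 7-day or prolonged abstinence.

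Cost: a few questions at a visit already planned, and a narrower claim for the verification.

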### Statistical analyses

Descriptive analyses will be conducted to examine whether randomization has resulted in an equal baseline distribution of participants regarding relevant characteristics across the two conditions using *χ*^2^-tests and *t*-tests. To account for any possible group differences at baseline, confounding variables will be included in subsequent analyses. We will use logistic regression models and analyses of variance to evaluate the effectiveness of the intervention by comparing smoking cessation rates across groups. Effect sizes, as well as confidence intervals, will be reported. To analyze abstinence rates, the intention-to-treat (ITT) approach will be used. This means that data of all randomized participants will be included in the analyses unless they are deceased or have moved to an untraceable address, as recommended by the Russell Standard criteria (RS) [28]. Participants with undetermined smoking status at follow-up will be counted as smokers. In addition to the ITT principles, a complete-case analysis will be performed, in which only participants with outcome data on all assessments will be included. As all assessments use a forced entry format, no imputation for missing values will be needed. All analysis will be conducted using the statistical program R and R Studio [47, 48].

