### Randomization

Randomization will be conducted by a research staff member. To ensure equal distribution of participants concerning selected key characteristics, randomization will be stratified based on four strata: number of cigarettes smoked per day (1–10/11–20/21–30/> 30 cigs per day), sex (female/male/diverse), age (18–30/ 31–64/> 64 years old) and level of education (low/middle/high) as reported by participants at baseline. The numbers of participants receiving each intervention are closely balanced within each stratum by performing a separate randomization procedure using permuted blocks (with each recruitment session as a block) of varying length. The first study participant per block (ordered randomly using the RAND function, Microsoft Excel) is randomized into the intervention group, the second one into the control group and so on. The randomization procedure is documented and maintained using a list which contains all possible combinations of strata and their levels as well as the number of participants in each group per strata combination. If the groups differ due to an imbalance in a certain strata combination (difference > 5 participants), the next participant with the respective strata combination will be allocated to the underrepresented group until an equal distribution is achieved.

Allocation concealment will be ensured, as participants will not be assigned to one of the study conditions until baseline measurements have been completed. Due to the nature of the intervention, neither participants nor staff can be blinded to allocation. In the study material, participants will be informed about the two study conditions. However, participants will be blinded to the study hypothesis in terms of which intervention is considered active.

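### The primary model's covariates appear to be chosen from baseline significance tests, which tends to omit the four stratification factors; a prespecified model should replace this

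*Protocol article*

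**What the plan says.** Under Statistical analyses, the protocol article plans descriptive analyses to "examine whether randomization has resulted in an equal baseline distribution of participants regarding relevant characteristics across the two conditions using" chi-square and t-tests. The next sentence reads: "To account for any possible group differences at baseline, confounding variables will be included in subsequent analyses". Neither sentence lists the variables, sets a threshold or defines a confounder.

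The model sentence follows: "We will use logistic regression models and analyses of variance to evaluate the effectiveness of the intervention by comparing smoking cessation rates across groups". It names no covariates.

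Under Randomization, "randomization will be stratified based on four strata: number of cigarettes smoked per day" (four levels), sex (three), age (three) and education (three). If the arms differ by more than five participants in a strata combination, "the next participant with the respective strata combination will be allocated to the underrepresented group until an equal distribution is achieved".

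The Covariates section lists variables that will be assessed but does not say which of them enter a model. Gender, age and education are in that list; cigarettes per day is not.

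**The concern.** Testing for balance and then adding variables to account for differences makes the test result the trigger for adjustment. After sound randomisation every baseline difference is a chance difference, so the tests carry no information on which variables predict quitting. A variable unrelated to quitting can enter, and a strong predictor that happens to be balanced stays out.

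The rule also works against the design. The four factors were considered important enough to stratify on and to correct by steering allocation. That makes them the variables least likely to show a difference, and so the least likely to be adjusted for.

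At stake is the primary result. In logistic regression the odds ratio changes with the covariates in the model, even balanced ones. The reported effect would therefore depend on which differences arose by chance and on what unblinded staff consider relevant or confounding. Leaving out the stratification factors also gives up a little precision.

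A smaller wording point: analysis of variance is named for comparing cessation rates, but abstinence is a yes/no outcome.

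**Working it through.** The plan gives no figure on this point to reproduce, and its sample-size calculation does not decide it.

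**Inputs from the protocol article:** 910 enrolled; 1:1 allocation; 5% significance level (sidedness not stated; two-sided assumed here); four stratification factors with 4 × 3 × 3 × 3 = 108 cells.

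**Assumed inputs:** the number of baseline variables tested (k), a 5% entry threshold, independence of the tests, the share of outcome variance explained by the strata (R²), and the effect sizes in the simulation.

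**Step 1: range for k.** The low end is a short list of 10. For the high end, I count 19 items in the Covariates section that can be measured at baseline. Four further items come from Table 1 (cigarettes per day, dependence, motivation, home restrictions), and five cognition and coping scales from Secondary outcomes: 19 + 4 + 5 = 28. Removing the four factors balanced by allocation leaves 24.

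**Step 2: chance of a spurious imbalance.** P(at least one) = 1 − 0.95^k; expected number = 0.05 × k.

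| k | P(at least one) | Expected number |
|---|---|---|
| 10 | 40% | 0.5 |
| 12 | 46% | 0.6 |
| 15 | 54% | 0.75 |
| 20 | 64% | 1.0 |
| 24 | 71% | 1.2 |

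Positive correlation between variables (craving, dependence and self-efficacy, for example) would lower these probabilities.

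**Step 3: size of a test that ignores the strata.** With the strata balanced, size = 2 × [1 − Φ(1.96 / √(1 − R²))].

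- R² = 0.05: 1.96 / √0.95 = 2.011, so size is 4.4%.
- R² = 0.10: 1.96 / √0.90 = 2.066, so size is 3.9%.

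A simulation with n = 910, four balanced binary factors and 10% quitting shows what such R² values require. Odds ratios of 1.65 per factor gave R² of 2.4% and size 4.9%. Odds ratios of about 2.2 for all four factors gave R² of 6.6% and size 4.4%.

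**Step 4: comparison of three models.** A second simulation used 3,000 trials per scenario and n = 910. Four binary factors were balanced within 16 cells. There were 12 other baseline variables, three of them prognostic at log odds ratio 0.3 per SD. The treatment log odds ratio was 0 (size) or 0.5 (power), and each stratification factor had log odds ratio 0.5 or 0.8.

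| Model | Size, 0.5 | Size, 0.8 | Power, 0.5 | Power, 0.8 |
|---|---|---|---|---|
| Unadjusted | 5.0% | 5.1% | 74.2% | 73.3% |
| Covariates selected by baseline p < 0.05 | 5.0% | 5.1% | 74.3% | 73.2% |
| Arm plus the four factors | 5.4% | 5.8% | 75.6% | 75.9% |

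The Monte Carlo standard error of the size figures is about 0.4 points, so 5.8% lies within two standard errors of 5%. The power gain from the fixed model over selection is 75.6 − 74.3 = 1.3 points and 75.9 − 73.2 = 2.7 points. Selection picked up at least one of the 12 other variables in 45 to 47% of trials, and never a stratification factor.

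**The case against.** The strongest reply is that the article never says a p-value decides entry. Confounding variables could be chosen on subject-matter grounds, and an analysis plan that is not shown may name them. The first part is right: selection by test is inferred from two adjacent sentences. It remains the natural reading, because inclusion is tied explicitly to group differences at baseline. A stated data-dependent rule is also more than a detail left for later.

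Second, the harm is small. This stands. Standard errors that are too wide make a test conservative, and the power at issue is a few points. Balance may also be looser than the calculations assume: 910 / 108 is about 8 participants per cell, and correction starts only when the difference exceeds five. So the factors are unlikely, not certain, to test as balanced, and the size of an unadjusted test moves back towards 5%.

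A reader might infer four stronger points that the document does not support:

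- **That selection inflates the type I error.** The simulation shows no material inflation.
- **That post-randomisation variables enter the primary model**, because the Covariates section includes "the use and acceptability of the received intervention (telephone counselling or self-help brochure"). That section says only that these are assessed. Adjustment is tied to baseline differences, and Table 1 collects received support and intervention use only at the post assessment, so the rule cannot select them.
- **That continuous secondary outcomes get analysis of variance on change scores.** The only sentence naming analysis of variance concerns cessation rates.
- **That 28 tests give a 76% chance of a spurious imbalance** (1 − 0.95^28). That count includes the four factors that allocation keeps balanced.

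**Conclusion.** The point holds and is worth correcting, at modest weight. As written, the covariates of the primary model depend on chance baseline differences, and the factors used in allocation tend to be omitted. At a 5% threshold, a model altered by chance is close to an even prospect or likelier over most of the range for k. The main cost is discretion over the primary odds ratio. The loss of efficiency is secondary, and the validity of the test is not in question.

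This rests on reading the two sentences as one rule, on independent tests, and on assumed prognostic effects; none of these is stated in the article. Naming analysis of variance for a binary outcome is a minor wording error.

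**What to change.** Amend Statistical analyses before the data are analysed:

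- For every abstinence outcome, specify logistic regression with arm plus cigarettes per day, sex, age and education as main effects.
- Say in advance how sparse levels are handled, since few quitters in a small level can cause separation. Either collapse them (for example diverse sex, more than 30 cigarettes per day, over 64 years) or enter cigarettes per day and age as continuous.
- State that baseline significance tests are not used to choose covariates, and present the baseline table descriptively.
- Remove analyses of variance as a method for comparing cessation rates.

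The cost is wording only: all four factors are reported at baseline, before allocation, and no new data are needed.

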## Methods

### Study design

The present evaluation is designed as a parallel-group, superiority, two-arm randomized controlled trial with 1:1 allocation ratio. The evaluation comprises three assessments within a period of approximately one year. Data collection will take place at baseline, three months (post assessment) and twelve months (follow-up assessment) after baseline assessment. The study design and participant flow are outlined in the Consolidated Standards for Reporting Trials (CONSORT) diagram (Fig. 1). After giving informed consent and completion of the baseline survey, participants will be randomly assigned to the intervention or control group. In the intervention group, participants will receive telephone counselling from counsellors of the national German Smokers Quitline, while in the control group they will be provided with a self-help brochure to support smoking cessation. Self-help materials were chosen as treatment in the control condition, as participants may have a benefit compared to receiving no intervention [20]. Moreover, it is considered unethical to recruit participants for a smoking cessation treatment when subsequently not offering an intervention. Providing an alternative intervention for the control group may also help achieve comparable response rates. To allow correction for any overreporting of abstinence, abstinence will be biochemically verified for a random sample of study participants who report abstinence at 12-month follow-up.

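### The complete-case analysis requires data at both follow-ups, so it drops known smoking statuses and conditions the 3-month comparison on 12-month response

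*Protocol article*

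**What the plan says.** Under Study design: "Data collection will take place at baseline, three months (post assessment) and twelve months (follow-up assessment) after baseline assessment". Under Primary outcomes, the first measure is "seven-day point prevalence abstinence at 3-month post and 12-month follow-up assessment", so the same outcome is analysed at two separate times. Prolonged abstinence is also primary, and Table 1 schedules it at 12 months only.

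Under Statistical analyses, abstinence is analysed by ITT: "data of all randomized participants will be included in the analyses unless they are deceased or have moved to an untraceable address". The missing-data rule is: "Participants with undetermined smoking status at follow-up will be counted as smokers". Next to this stands a second, complete-case analysis, for which "only participants with outcome data on all assessments will be included". Imputation is ruled out: "As all assessments use a forced entry format, no imputation for missing values will be needed".

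On attrition, Data collection and management says: "It is expected that the rate of loss-to-follow-up will not exceed the calculated 30" per cent. The article does not split this figure by time point or by arm.

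**The concern.** Randomisation follows the baseline survey, so everyone randomised has baseline data. The all-assessment condition therefore means that both the 3-month and the 12-month questionnaire were answered. Someone with a recorded 3-month status who misses month 12 leaves the 3-month complete-case analysis. Someone with a recorded 12-month status who missed month 3 leaves the 12-month one.

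The purpose of a complete-case analysis here is to show how far the result depends on counting non-responders as smokers. Nothing else stated in the article does this. The forced-entry format prevents skipped items but does not supply a questionnaire that was never returned. As worded, the check changes two things at once: it lifts the missing-equals-smoking rule, and it restricts the sample to people who answered twice. If its result differs from ITT, the reader cannot tell which change is responsible. The 3-month comparison is also conditioned on something that happens nine months later, which both relapse and trial arm could affect.

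**Working it through.** **The plan's own figure.** Sample size calculation: 700 × 1.3 = 910, which reproduces the stated total. If 30% are lost by month 12, 910 × 0.70 = 637 respond there. The article gives no other response figure, so every 3-month rate below is an assumption.

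**Outcomes discarded at 3 months.** Let r3 and r12 be the response proportions. The all-assessment set is the overlap of the two groups of responders. It lies between 910 × max(0, r3 + r12 − 1) and 910 × min(r3, r12). The upper bound is purely progressive dropout, where everyone who answers at 12 months also answered at 3. With r12 = 0.70 and progressive dropout, the set holds 637:

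| r3 (assumed) | Known at 3 months | Discarded | Share | Interval ratio √(known/637) |
|---|---|---|---|---|
| 80% | 728 | 91 | 12.5% | 1.07 |
| 85% | 774 | 137 | 18% | 1.10 |
| 90% | 819 | 182 | 22% | 1.13 |

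If dropout is not progressive, more is lost. At the lower bound of the overlap, 273 known 3-month outcomes are discarded in each row, because 910 × (1 − 0.70) = 273.

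The interval ratio assumes that those discarded have about the same abstinence rate as those kept.

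**Outcomes discarded at 12 months.** Under progressive dropout, none. If non-response at 3 months is instead independent of response at 12 months and equals 10%, 20% or 30%, then 637 × 0.90, 0.80 or 0.70 = 573, 510 or 446 are kept. The losses are 64, 127 or 191, with interval ratios of 1.05, 1.12 or 1.20.

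**When selection biases the odds ratio.** Let p be 3-month abstinence among 3-month responders in one arm, and let ra and rn be 12-month response among that arm's 3-month abstainers and smokers. The rate in the all-assessment set is p·ra / (p·ra + (1 − p)·rn). The odds in each arm are therefore multiplied by ra/rn, and the odds ratio by (ra/rn, intervention) ÷ (ra/rn, control). All rates here are assumed:

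- Later response unrelated to status (87.5% throughout): the factor is 1. The rates and the odds ratio are unchanged.
- Response of 95%/85% (abstainers/smokers) in both arms: the factor is 1. True rates of 20% and 14% become 21.8% and 15.4%, and the odds ratio stays at 1.54.
- Response of 95%/80% in the intervention arm and 90%/88% in the control arm: the factor is (0.95/0.80) ÷ (0.90/0.88) = 1.1875 ÷ 1.0227 = 1.16. With 14% in both arms, the set shows 16.2% and 14.3%, an odds ratio of 1.16 where it should be 1.00. With 20% and 14%, the odds ratio moves from 1.54 to 1.78.

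The odds ratio is distorted only in the third case, where dependence on 3-month status differs by arm.

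**The case against.** The analysis is supplementary. ITT is the stated analysis of abstinence and its sample does not depend on this wording. All the data are collected anyway, so an analysis by time point remains possible whatever the text says.

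Requiring data at every assessment is also a recognised meaning of complete case. It gives one fixed group in which 3- and 12-month abstinence can be compared without a changing denominator, which suits a trial interested in both short- and long-term effects. A reader might infer that the known outcomes are discarded for no benefit. That is too strong, because the common sample has some descriptive value.

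The design also works to keep response similar across arms. The control arm receives an active alternative partly for that reason, vouchers are paid at each assessment, a raffle rewards completing the whole study, and reminders are used. The 30% is a ceiling, so taking it as the actual 12-month loss is pessimistic. The interval ratios sit uneasily with the selection argument: the precision of a log odds ratio depends mainly on the number of abstainers, so if those lost later are mostly smokers, the widening is smaller than shown. Finally, the article is condensed, and a full protocol or analysis plan may contain further missing-data analyses.

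These points limit the size and weight of the concern. They do not remove it: the rule is stated, nothing elsewhere in the article qualifies it, and the one stated check still changes two assumptions together. The design features do not settle arm-related response either. The arms differ in counsellor contact, nobody is blinded to allocation, and only controls are offered counselling at the end of the study.

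**Conclusion.** The point holds in a limited form and is worth correcting. It is certain from the wording that anyone who misses one follow-up is removed from the complete-case analysis of the other, and that this set therefore cannot isolate the effect of counting non-responders as smokers.

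The number lost is not known. The figure of 91 to 182 known 3-month outcomes rests on assumed response of 80–90% at 3 months, 70% at 12 months and progressive dropout. The 7–13% widening rests additionally on similar abstinence rates among those discarded. At 12 months the loss may be zero, and the complaint then falls away for that outcome.

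A reader might infer that the 3-month treatment effect will be biased, or that the trial's main result is compromised. The documents support neither. The ITT result is unaffected, and bias in the complete-case odds ratio needs later response to depend on 3-month status differently by arm, for which the article gives no figures. The odds ratios of 1.16 and 1.78 show what could happen and are not estimates.

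**What to change.** Replace the all-assessment condition with one sentence that defines complete cases separately for each outcome and time point. The analysis would include every randomised participant whose smoking status is recorded at the time point analysed, whether or not the other follow-up was completed. For prolonged abstinence, which is assessed at 12 months, the same rule applies at that assessment. If a common sample is wanted to describe change over time, keep the all-assessment set as an additional analysis labelled as such.

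This needs no new data and leaves the ITT analysis as it is. The cost is that the 3- and 12-month complete-case tables will have different denominators, which should be shown by arm.
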